### Who will take informed consent? {26a}

After admission to the rehabilitation clinic, the patient will be contacted either by the corresponding physician (ward or head physician) or other healthcare workers (nurse, therapist, or scheduler). The first member to contact the patient will inform him/her about the study and hand the flyer with the written information. Furthermore, the physician conducting the initial clinical examination will decide whether the patient is eligible for the study. If eligible, an appointment with the study therapist will be scheduled. The therapist will then explain the details of the study and take the informed consent of the patients who agree to participate.

### Additional consent provisions for the collection and use of participant data and biological specimens {26b}

Not applicable. The informed consent includes the provision for the collection of all participant data stated in the protocol. No biological specimens are contemplated at the time of this protocol.

## Interventions

### Explanation for the choice of comparators {6b}

The intervention group will receive a home-based exercise program after an initial center-based training. Currently, in Germany, there is no offer of a home-based program, which would allow patients a soft transition from the rehabilitation clinic to their everyday life. Likewise, rural areas have difficulty accessing the programs implemented exclusively in rehabilitation centers and clinics [13, 15].

In line with recent studies, diverse therapy modules tailored to individual patient needs, when based on an early screening for psychosocial risk factors, enable an optimal therapy for chronic back pain [10, 16, 17]. Accordingly, an initial differentiation between low-risk (unimodal) and high-risk (multimodal) groups through the RSI score, followed by an additional module individualization by the RPI-S score, is encouraged [11].

The intervention incorporates behavioral therapy modules together with exercise in the multimodal group. A combined approach of sensorimotor training, deflection, and body scan targets neurobiological adaptation processes. Furthermore, psychoeducation involving caregivers increases compliance and dismantles unfavorable support structures in the social environment [17].

The control group will receive the current rehabilitation aftercare offered by the German pension insurance “DRV” in the rehabilitation centers. It is relevant and appropriate to compare the new program with the “treatment as usual” program already implemented.

### Intervention description {11a}

#### Intervention group

The intervention has a total duration of 12 weeks. During the first 3 weeks, the training takes place within the clinic, three times per week, 30 min per session (3 weeks supervised center-based). In the following 9 weeks, the participant continues the training program independently at home with the help of training materials (diary, videos, mat, and block). In case of questions, the study therapist can be contacted via telephone during the 9-week home-based intervention.
Intervention arm I (unimodal): The low-risk group (unimodal) receives sensorimotor training exclusively. The Sensorimotor Training Program (SMT) consists of four exercises (quadrupedal/all-fours stability, deadlift/rowing, double leg–single leg heel-pad stance, and side planks) performed in three sets of ten repetitions each. All exercises train the muscles surrounding the torso, two exercises initiate this training by an impulse via the extremities. The program contains 12 ascending levels of difficulty to enable individualized and adaptive use. At the beginning, the study therapist determines participants’ entry level depending on the individual training condition. Ideally, the level of difficulty would increase by one level weekly through the use of additional loads and unstable material. If not possible, the training will continue for another week at the existing difficulty level. More details on the sensorimotor training program are provided in Table 1 [15].

**Table 1 Tab1:** Sensorimotor training program (SMT) exercises levels 1 to 12

Exercise 1: quadrupedal/all-fours stability		Exercise 2: deadlift/rowing		Exercise 3: double leg–single leg heel-pad stance		Exercise 4: side planks	
Stable ground	Unstable ground	Stable ground	Unstable ground	Stable ground	Unstable ground	Stable ground	Unstable ground
1. Hand and knee stance: cat’s hump/horse’s back 2. Hand and knee stance diagonal arm and leg: from body center upwards (horizontal) 4. Hand and feet stance: bending, stretching a leg 6. Hand and feet stance: release arm, trunk rotation	3. Hand and knee stance diagonal arm and leg: from body center upwards (horizontal) 5. Hand and feet stance: bending, stretching a leg 7. Hand and feet stance: release arm, trunk rotation 8. Planks: leg horizontal 9. Planks: diagonal leave arm and leg 10. Planks: leave arm, rotate the trunk 11. Planks: leave arm and diagonal leg, rotate trunk 12. Press-up: leave arm	1. Rowing plus additional weight 3. Rowing in ball stance plus additional weight 5. One-handed rowing plus additional weight 6. One handed rowing plus additional weight in ball stance 9. One-handed rowing plus additional weight in single-leg stance 10. One-handed rowing plus additional weight in single leg ball stance	2. Rowing plus additional weight 4. Rowing in ball stance plus additional weight 7. One-handed rowing plus additional weight 8. One-handed rowing plus additional weight in ball stance 11. One-handed rowing plus additional weight in single-leg stance 12. One-handed rowing plus additional weight in single-leg ball stance	1. Bipedal: heel-pad stance 3. Unipedal stance plus hip abduction 4. Unipedal stance plus hip abduction and leg extension 6. Unipedal ball stance plus hip abduction and leg extension 10. Unipedal squat 11. Unipedal squat plus additional weight	2. Bipedal: heel-pad stance 5. Unipedal stance plus hip abduction and leg extension 7. Unipedal ball stance plus hip abduction and leg extension 8. Squat in ball stance 9. Squat in ball stance and hip bending 12. Unipedal squat plus additional weight	1. Knee on the ground: hip up/down 3. Knee on the ground: hip released from the ground and hold 5. Knee on the ground: hip up/down without putting down the pelvis 7. Legs stretched, hip fixed upwards 10. Legs stretched, release leg from the ground 12. Legs stretched, release leg and diagonal arm from the ground: horizontal contact	2. Knee on the ground: hip up/down 4. Knee on the ground; hip released from the ground 6. Knee on the ground: hip up/down without putting down the pelvis 8. Legs stretched, hip fixed upwards 9. Legs stretched, hip up/down 11. Legs stretched, release leg from the ground

Source: Adapted from Niederer D, Vogt L, Wippert P-M, Puschmann A-K, Pfeifer A-C, Schiltenwolf M, et al. Medicine in spine exercise (MiSpEx) for nonspecific low back pain patients: study protocol for a multicentre, single-blind randomized controlled trial. Trials. 2016;17 [1]:507

Interventional exercises details. For each exercise, level [1–12], surface (stable/instable), and description are provided; p. 6Intervention arm II (multimodal): The RPI-S score gives information about the type of individualized care required for patients in the high-risk group (multimodal). Along with the SMT, the multimodal group receives supplementary behavioral therapy modules. Multimodal intervention incorporates three behavioral therapy modules (BT)**.** The modules are patient education, cognitive distraction techniques, and the “body scan” (element from the Mindfulness-Based Stress Reduction Program [18]). Depending on their RPI-S risk profile, participants receive one of the following intervention module combinations:Sensorimotor training + patient educationSensorimotor training + body scan + patient educationSensorimotor training + distraction module + patient educationSensorimotor training + distraction  module + body scan + patient education

Additionally, patients could receive a questionnaire for a person they feel close to, mainly in order to give them support during the implementation of aftercare exercises.

##### Patient education

A multipart film (four parts, duration of more than 2 h) conveys knowledge on the topic of general pain, development and maintenance of pain, active pain control, pain regulation, and how to deal with everyday life pain incompatible processes. The patient education film also includes strategies for self-empowerment in pain management through interactive reflective exercises, exchange with the partner, and active approaches. It will be delivered to all patients allocated to the multimodal group at the beginning of the intervention.

##### Cognitive distraction

The cognitive distraction module was adapted to the various sensorimotor training exercises and proceeds parallel to the physical training [19]. The cognitive distraction task consists of the n-back task (memory working task, once with numbers and once with colors) and a word list assignment [20–22]. Adjustment of the level of difficulty according to the individual’s ability and needs is also available. The study therapist indicates at the beginning that one movement corresponds to one word or digit heard. Ten movements take place with a 30-s break between the individual sets of each exercise. At the start and end of the training set, a signal announces the movement execution.

##### Body scan (element from Mindfulness-Based Stress Reduction Program)

Four versions of body scans based on the “Mindfulness-Based Stress Reduction” Program [18, 23–25] together with an introduction about mindfulness constitute one of the behavioral therapy modules. The body scans are presented on the DVD invariably after the sensorimotor training exercises.

At the beginning, the therapist advises patients on the practice of mindfulness exercises and introduces them to the first body scan. The therapist points out the importance of continuous regular practice and patience, guiding the patient to listen to it in either a sitting or lying position. Further they give the patient sufficient time in a quiet warm atmosphere, allowing a comfortable and safe starting position. The body scans comprise a longer version (Nr.1), a shorter one, and different levels of difficulty as the program progress (Nr. 2 to 4).

##### Close person support in the implementation of aftercare exercises and questionnaire

Multimodal patients with RPI-S high-risk scores in the domains “social environment” and/or “medical care environment” will be informed about the close person questionnaire, which is designed and conducted by the MLU Halle-Wittenberg. If the participant agrees, at T0, the study material will be sent in a pre-stamped envelope to a person they feel close to (usually a spouse, partner, child, or best friend). The close person receives information about the study, the declaration of informed consent, the questionnaire, and information on how to support the patient regarding physical activity. If they agree to participate, the completed questionnaire and one copy of the declaration of informed consent in a pre-stamped envelope will be sent to the MLU Halle-Wittenberg. At T2, a follow-up questionnaire will be sent to the same close person.

The questionnaire (sent at T0 and T2) is based on a previous study [26]. It incorporates items regarding given support (of physical activity/aftercare exercises) and social distress from the Berlin Social Support Scale  [27] and the social support scales for illness (SSUK) [28]. Likewise, it includes resources, barriers, and the importance of physical activity, as well as the age, gender, and health status of the close person.

#### Control group

Patients in the control group receive the standard aftercare treatment for back pain in rehabilitation centers (“treatment as usual”). This comprises the “T-RENA,” “IRENA,” and “Reha-Sport” programs of Germany.

T-RENA is a unimodal rehabilitation aftercare program suitable for persons with impairments or functional limitations on the postural and locomotor system. It is a training supported by the use of equipment carried out in groups of up to 12 people, usually containing 26 units of 60 min each. T-RENA includes preparatory exercises for subsequent muscle building training (e.g., general endurance training, general strength training), mobility, coordination, strength, and endurance. Moreover, it aims to develop and consolidate basic motor patterns together with daily life activities, also training on compensation techniques [29].

IRENA refers to a multimodal aftercare group service for 10–12 participants. It includes up to 24 units lasting at least 90 min each. IRENA is indicated when there are persistent functional and/or cognitive limitations, the need of lifestyle stabilization, and behavioral changes, further when support on specific workplace and professional reintegration problems is required and in the transfer of skills learned at rehabilitation. Therapy is provided in at least two of the following listed services: sports and exercise therapy (endurance or muscle-building training), physiotherapy (including spinal gymnastics), motivation guidance (promotion of behavioral changes), nutrition (nutritional counseling), psychology (stress management, relaxation training, problem-oriented group work), and social work (including professional orientation). In the case of orthopedic diseases (such as chronic back pain), the services offered usually include physiotherapy, sports and exercise therapy, and group psychological work for pain management [29].

Reha-Sport consists of gymnastics, athletics, swimming, and group exercise games, which are carried out in fixed groups with a trainer. It does not include equipment training, and the duration of a unit is at least 45 min [29].

The focus of these three aftercare rehabilitation programs (T-RENA, IRENA, and Reha-Sport) is on physiotherapy, movement, and behavioral therapy modules; however, they lack personalization of therapy content regarding individual needs. Furthermore, all three are conducted in an ambulatory setting and follow the routine of the German Pension Insurance aftercare program.

At the end of the rehabilitation at the clinic, one or none of the aftercare programs is recommended [29]. If the patient is unable to attend the rehabilitation center, the patient does not receive any aftercare treatment.

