Furthermore, psychosocial factors play a significant role in the development of chronic pain syndromes [7], including low back pain [8]. In line with the biopsychosocial model, LBP is better explained by the interaction between psychological, physical, and social factors than by the single anatomical or physiological model [9]. According to the national health care guidelines for the diagnosis and treatment of non-specific low back pain recommendations [10], an early screening of psychosocial risk factors is vital for an optimal therapy design (unimodal vs. multimodal). Until now, a lack of practical screening instruments for the early identification of individual needs regarding exercise interventions has been described. The recently published screening tool named Risk Stratification Index (RSI) [11] enables an estimation of the chronicity risk by means of psychosocial factors, supplemented by the Risk Prevention Index (RPI-S). The RPI-S additionally allows the identification of risk components in four psychosocial areas (pain experience, stress, medical care context, care context) [11]. Both screening tools aim to inform about the individual need for further psychosocial services and if specific supplementary training, physiotherapy, and/or psychosocial components are needed in order to increase intervention efficiency [12].

In rehabilitation ambulatory care, a multidisciplinary approach combining medical, physiotherapeutic, and psychological fields has already been introduced in Germany. However, its application has been challenging in diverse areas, and individualization of the therapy is still missing [10]. Its implementation has not reached most rural areas [10] and has to date been limited only to rehabilitation clinics and centers [13]. More often, no rehabilitation center is located in areas with low infrastructure; hence, the offer is missing in around 60% of the cases in Germany [10, 13, 14]. Until now, aftercare measures have been underused or were not easily accessible [14]. To our knowledge, no offer of an individualized home-based rehabilitation program is available. It is therefore of the greatest interest to assess these programs in the context of rehabilitative measures.

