### Objectives {7}

This is a study on rehabilitation aftercare for back pain patients.

The aim of the study is to evaluate whether and how well an individually tailored rehabilitation aftercare program for back pain patients works. The following hypotheses are going to be examined:
An individualized and home-based aftercare program is more effective than regular outpatient rehabilitation aftercare in terms of pain reduction.An individualized and home-based aftercare program is more effective than regular outpatient rehabilitation aftercare in terms of work ability.An individualized and home-based rehabilitation aftercare leads to better patient compliance and more sustained intervention effects than regular outpatient rehabilitation aftercare.An individualized and home-based rehabilitation aftercare could be implemented and incorporated long term (feasibility) in the regular rehabilitation aftercare routines of the German Pension Insurance.

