### Trial design {8}

Multicenter intervention trial: A randomized controlled prospective longitudinal intervention study (RCT) will be conducted at several hospitals in the regions of Berlin-Brandenburg and Central Germany. The study includes a total of four measurement points: at rehabilitation clinic admission (t0: baseline), at the end of the rehabilitation stay (t1), at the end of the 9-week home training phase (t2), and 3 months after the end of the accompanied training (t3: follow-up). Questionnaires and functional and clinical data are collected. After signing the informed consent, patients will be randomly allocated to the intervention group (including 2 subgroups arms; unimodal and multimodal intervention) or the control group (treatment as usual) using a 2:1 ratio. The subgroup allocation within the intervention group, either to a unimodal or a multimodal therapy will follow the Risk Stratification Index (RSI) [11]. An additional assignation to modules within the multimodal group will follow the Risk Prevention Index (RPI-S) [11] (see Figs. 1, 2, and 3.). The initial random 2:1 ratio allocation should ensure enough patients in each subgroup arm (unimodal or multimodal) to be able to analyze the differences between both and confirm the discrimination’s ability of the screening tool in this population (see Fig. 4). The framework of the trial is superiority.

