### Relevant concomitant care permitted or prohibited during the trial {11d}

Concomitant care is allowed during the trial.

The trial setting is the rehabilitation clinic and home. Therefore, no broader supervision is possible or intended. The study has a pragmatic approach with the aim of allowing the patient to function in his or her real context. At T0 and T3, the actual medications (prescribed or not prescribed) will be recorded.

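### A positive result would show superiority over usual aftercare provision, which includes no aftercare, and not over regular outpatient aftercare as hypotheses 1 to 3 state

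*Protocol article*

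**What the plan says.** Objectives {7} sets out the first hypothesis as "An individualized and home-based aftercare program is more effective than regular outpatient rehabilitation aftercare in terms of pain reduction". Hypotheses 2 (work ability) and 3 (compliance and sustained effects) name the same comparator, and the Discussion gives the comparison with regular outpatient care as the main purpose. Trial design {8} adds: "The framework of the trial is superiority".

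The Control group section under Intervention description {11a} opens in line with this: "Patients in the control group receive the standard aftercare treatment for back pain in rehabilitation centers". It then describes T-RENA, IRENA and Reha-Sport. At its end it says that, when the clinic stay finishes, "one or none of the aftercare programs is recommended", and continues: "If the patient is unable to attend the rehabilitation center, the patient does not receive any aftercare treatment".

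Explanation for the choice of comparators {6b} calls the control treatment as usual and defends it as the programme already in place. Section {20c} plans an intention-to-treat analysis with a per-protocol sensitivity analysis. Section {11d} states: "Concomitant care is allowed during the trial".

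**The concern.** The section that defines the control arm says two different things. Its first line has every control patient receiving standard aftercare. Its last lines have some receiving none, either because none was recommended or because they could not get to a centre. The eligibility criteria do not require that a patient could attend one. The control arm is therefore a mixture of aftercare and no aftercare in unstated proportions, while the hypotheses name only the first component.

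Under intention to treat, a difference between the arms can come wholly from the untreated part of the control arm. A programme no better than T-RENA, IRENA or Reha-Sport could then be reported as more effective than they are. This matters for the decision the trial is meant to inform. The Dissemination plans foresee adoption into the regular aftercare of medical rehabilitation, and filling gaps in the existing offer is a different decision from replacing an offer that has been outperformed. For hypothesis 3 there is a further difficulty: a control patient with no programme has nothing to comply with.

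**Working it through.** **1. Which contrast is estimated.** Let p be the share of control patients with no aftercare, e the effect of the home programme against nothing, and δ its advantage over regular aftercare. If all intervention patients get the home programme, the expected difference between the arms is

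(1 − p)·δ + p·e.

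Hypotheses 1 to 3 are about δ. The intention-to-treat comparison estimates the whole sum. With δ = 0 it is p·e, which is above zero whenever p and e are.

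**2. Inputs.**
- From Sample size {14}: design effect d = 0.2, alpha 5% (taken here as two-sided), correlation 0.57, three time points, 843 patients analysed, 562 of them in the intervention arm. The printed control arm of 289 does not fit that total (562 + 289 = 851), so 843 − 562 = 281 is used. With 289, the 69% below becomes about 70%.
- Assumed, because the protocol gives neither: p from 10% to 60%, and e = 0.3 SD.

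**3. Standard errors, in SD units.**
- Plain two-sample comparison: √(1/562 + 1/281) = 0.0731.
- Repeated-measures variance, averaging three measurements: SD = √((1 + 2 × 0.57)/3) = 0.845, so SE = 0.845 × 0.0731 = 0.0617. This treats the difference as present at all three visits, which is generous because none is expected at T0. A baseline-adjusted comparison, with SD = √(1 − 0.57²) = 0.822, gives nearly the same results: 17%, 32% and 85% at p = 20%, 30% and 60%.

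**4. Chance of a significant result in the programme's favour when δ = 0.** The probability is Φ(p·e/SE − 1.96), with e = 0.3.

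| p | p·e | z (plain) | Plain | Repeated measures |
|---|---|---|---|---|
| 10% | 0.03 | 0.41 | 6% | 7% |
| 20% | 0.06 | 0.82 | 13% | 16% |
| 30% | 0.09 | 1.23 | 23% | 31% |
| 60% | 0.18 | 2.46 | 69% | 83% |

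With p = 0 the figure would be 2.5%. The result also depends on e: at p = 30%, the plain test gives 13% with e = 0.2 and 54% with e = 0.5.

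**5. What it takes to reach the full design effect with δ = 0.** Setting p·e = 0.2 gives e = 0.2/p: 2.0 SD at p = 10%, 1.0 at 20%, 0.67 at 30% and 0.33 at 60%. With a small untreated share, the mixture alone cannot plausibly produce the planned effect. With a large share it can.

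**6. Can the described measurements separate the cases?** Table 2 collects the aftercare recommendation from the discharge report, but a recommendation is not attendance. Patient compliance and acceptance asks all participants at T2 and T3 how often they do their aftercare exercises. A patient exercising alone and one attending a group could give the same answer. The training journal goes to the intervention arm only (section {11c}). The article describes no item on which programme was attended or for how many units. Because concomitant care is open, the same gap applies to intervention patients who also attend a centre programme.

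**The case against.** The strongest reply is that treatment as usual was chosen openly. Section {6b} justifies it, section {11d} calls the approach pragmatic, and the trial's rationale is to reach patients whom centre-based aftercare does not reach. Non-receipt among controls is then part of the policy being compared, and intention to treat validly estimates the effect of offering the home programme against the existing offer. This stands, and the control arm need not change. It does not rescue the wording of the hypotheses, which name a different comparator.

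Four stronger readings are tempting, and the document does not support them.

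- *About 60% of controls will be untreated.* The Background does say "hence, the offer is missing in around 60% of the cases in Germany", but this is national background tied to areas with low infrastructure. It is not a forecast for patients at the six clinics. The 60% row is one end of a range.
- *Attendance is not recorded.* The recommendation and the exercise frequency are collected in both arms, and the questionnaires are not reproduced in the article. It can be said only that no item on programme and units is described.
- *Controls are compared in mid-course at T2.* T-RENA is described as "usually containing 26 units of 60 min each", and 26 units in the 9 weeks from discharge to T2 would need 26/9 = 2.9 per week. But no weekly frequency is given, IRENA's 24 units are a maximum, Reha-Sport has no count, and the primary ANOVA also includes T3.
- *The superiority claim should depend on an analysis weighted for attendance.* Ability to attend is likely to be related to prognosis, and baseline covariates may not capture that. Such a condition would let a non-randomised comparison overrule a randomised one.

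**Conclusion.** The concern holds as a mismatch between claim and comparator, not as a fault in the choice of control. As the article stands, a significant primary result supports superiority over usual aftercare provision, including none. It does not by itself support superiority over T-RENA, IRENA or Reha-Sport, although hypotheses 1 to 3 and the Discussion would have it read that way.

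How much this matters turns on the share of controls without aftercare, which the protocol does not give. For a programme with no advantage over regular aftercare, the illustrated chance of a significant result runs from 6–7% with one control in ten untreated to 69–83% with six in ten. These figures rest on the assumed 0.3 SD over nothing, on all intervention patients receiving the programme, and on 562 and 281 analysed patients. They show the mechanism and its sensitivity, and do not predict this trial's result. The point should be corrected before results are reported.

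**What to change.** 1. Reconcile the opening and the end of the Control group section, so that it is clear that the arm receives whatever usual provision offers, including nothing.
2. Restate hypotheses 1 to 3, the main purpose in the Discussion and the planned conclusion as *versus usual aftercare provision, including no aftercare*.
3. If the questionnaires do not already hold it, add one item at T2 and T3 in both arms: the aftercare programme attended (T-RENA, IRENA, Reha-Sport, other, none) and the number of units.
4. Report receipt by arm beside the primary result, so that readers can see how much of the control arm had aftercare.
5. Label any comparison with aftercare actually received as supportive and non-randomised. It should not be a condition for the primary claim. A subgroup defined at baseline by access to a centre would keep the randomised comparison within it.

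The cost is some rewording, one questionnaire item and one descriptive table. The claim becomes narrower. Recruitment and follow-up were already running at this protocol version, so a new item would be missing for patients who had passed T2 or T3. For them, only the discharge recommendation and the exercise-frequency answer described in the article would be available.
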